#### Health-related quality of life

Participants’ self-reported health-related quality of life will be assessed through the Swedish version of the EQ-5D-5L.^34 44^ This validated questionnaire consists of two parts, the EQ-5D descriptive system and the EQ visual analogue scale (EQ VAS). The descriptive system is divided into five dimensions with one question for each dimension. The five dimensions are: mobility, self-care, usual activities, pain/discomfort and anxiety/depression. The five-level version has five response levels for each dimension: no problems, slight problems, moderate problems, severe problems and extreme problems/unable to. The second part of the questionnaire consists of a VAS on which the respondents rate their perceived health from 0 (being the worst imaginable health) to 100 (being the best imaginable health). Despite the lack of medication-related questions, the EQ-5D is one of the most frequently used generic instruments for evaluating the impact of pharmacist interventions on health-related quality of life.^45^

#### Beliefs about medicines

Participants’ beliefs about medicines will be assessed through the Swedish version of the Beliefs about Medicines Questionnaire (BMQ).^35^ This validated questionnaire consists of two sections, BMQ-General and BMQ-Specific. BMQ-General assesses the respondents’ beliefs about medicines in general and BMQ-Specific evaluates beliefs about medicines prescribed for the respondents’ personal use. BMQ-General consists of three subscales (*harm, overuse* and *benefit*), while BMQ-Specific consists of two subscales (*necessity* and *concern*). The questionnaire consists of 22 questions that are scored on a five-item Likert scale: 1=strongly disagree, 2=disagree, 3=uncertain, 4=agree and 5=strongly agree.

### Semi-structured interviews

Semi-structured individual interviews will be conducted with participants and healthcare professionals after completion of the telepharmacy service. An interview guide will be used, and the questions will mainly focus on the respondents’ experiences and attitudes towards this telepharmacy service. The interviews will be conducted by a trained interviewer in the research group who is not directly involved in the telepharmacy service.

### Data analysis and statistics

Descriptive statistics, for example, frequencies and proportions, will be used to present MRPs. Due to the single-arm design, no comparative analyses will be performed.

Self-reported medication adherence, beliefs about medicines and health-related quality of life will be compared between baseline and the end of the study using appropriate statistical methods. Regarding self-reported medication adherence, an increase of approximately 10 percentage points is expected. Regarding beliefs about medicines, a moderate increase is expected for positive beliefs (benefit and necessity), while a moderate decrease is expected for negative beliefs (harm, overuse and concern). Regarding health-related quality of life, a moderate positive change is expected. Statistical analyses will also be performed to investigate associations between beliefs about medicines and self-reported medication adherence and various demographic factors such as age, sex and number of medications.

Regarding the semi-structured interviews, the interviews will be audio-recorded, transcribed verbatim and analysed using reflexive thematic analysis.^46 47^

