### Sample size

The aim is to include 100 participants. This sample size serves the dual purpose of describing the prevalence of MRPs within the study population with good precision and enabling the statistical evaluation of changes in key outcome measures (eg, self-reported medication adherence, measured dichotomously) from baseline to the end of the study through intra-individual comparisons. No comparison group is included.

A priori power calculation has been performed to size the study with respect to the intra-individual comparison of the proportion of adherent participants. Based on the assumptions of a clinically relevant increase in the proportion of adherent participants from 85% at baseline to 95% at the end of the study (ie, an absolute difference of 10 percentage points), and an expected correlation (phi coefficient) of 0.6 between the two measurement time points, 80 participants are required to achieve 80% statistical power to detect this difference using a two-sided McNemar’s test at a 5% significance level (α=0.05), with continuity correction applied. The assumptions about the proportions of adherent participants are based on results from previous studies on self-reported medication adherence using the Medication Adherence Report Scale (MARS-5) questionnaire.^36 37^

Since the planned inclusion is 100 participants, which exceeds the calculated requirement of 80, the study will have >80% power to identify a difference of this magnitude under the given assumptions. The sample size also accounts for a potential dropout rate of 20%. The sample size of 100 participants is therefore considered well-justified and adequate to meet the study’s descriptive aims and allow for meaningful analyses of changes over time.

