#### Medication adherence

Participants’ self-reported medication adherence will be assessed through the Swedish version of the MARS-5.^33 42^ This validated questionnaire consists of five questions describing non-adherent behaviour that is scored on a five-item Likert scale: 1=always, 2=often, 3=sometimes, 4=rarely and 5=never. The sum score ranges between five and 25 points, where a higher score indicates higher levels of self-reported medication adherence. MARS-5 scores will be dichotomised into adherent/non-adherent. The cut-off score will be >22, in accordance with previous studies.^36 43^

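### Associations with adherence would, on the natural reading, use MARS-5 cut at >22, leaving about 15 non-adherent participants and losing power against the 5–25 score already collected

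*Protocol article*

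**What the plan says.** Data analysis and statistics announces: "Statistical analyses will also be performed to investigate associations between beliefs about medicines and self-reported medication adherence and various demographic factors such as age, sex". Medication count is listed as a further factor. The section gives no model, outcome variable, time point or form of MARS-5 for these analyses.

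The Medication adherence section describes a sum score from 5 to 25, higher meaning more adherent, and then fixes the form to be used: "MARS-5 scores will be dichotomised into adherent/non-adherent. The cut-off score will be >22, in accordance with previous studies". Sample size also treats adherence as binary, though there it is speaking of change within participants. It assumes a rise in the adherent share "from 85% at baseline to 95% at the end of the study" and states: "The aim is to include 100 participants". The abstract names McNemar's tests for the questionnaire outcomes. Nowhere does the article describe an analysis of the MARS-5 sum score.

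**The concern.** A cut at >22 suits a before-after comparison of proportions, which is what the study was sized for. It does not suit a between-person association. Scores of 23, 24 and 25, which the plan expects 85% of participants to have, become identical, and so do all scores from 5 to 22. The contrast then rests on the few people below the cut.

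At stake is how a null result would be read. If beliefs about medicines and adherence are moderately related, a finding of no association could be produced by the cut alone, although the data to avoid this are already on the questionnaire.

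**Working it through.** **The plan's own figure.** Sample size states that "80 participants are required to achieve 80% statistical power to detect this difference", with "an expected correlation (phi coefficient) of 0.6 between the two measurement time points" and a two-sided McNemar test "at a 5% significance level (α=0.05), with continuity correction applied".
- Joint probability of being adherent both times: 0.85×0.95 + 0.6×√(0.85×0.15×0.95×0.05) = 0.8075 + 0.0467 = 0.8542.
- Discordant cells: 0.95 − 0.8542 = 0.0958 and 0.85 − 0.8542 = −0.0042. Their sum is ψ = 0.0916, and d = 0.10.
- n = (1.96√ψ + 0.8416√(ψ − d²))²/d² = 69.5.
- With continuity correction: (69.5/4)×(1 + √(1 + 2/(69.5×0.10)))² = 79.2, so 80 reproduces.

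One discordant cell is negative because phi cannot exceed √(0.85×0.05/(0.15×0.95)) = 0.546 with these margins. That is a separate matter for the sample size section and does not affect what follows, which uses only the 85% and the 100.

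**Size of the smaller group at baseline.** 0.15×100 = 15 non-adherent (binomial 95% range 8 to 22). With 80 participants it would be 0.15×80 = 12. Recruitment of study participants says that the baseline questionnaires come back with the consent form, so a baseline association need not lose later dropouts. N = 100 is therefore the natural case and 80 a lower one.

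**Analytic check.** For a normal score cut at 15/85, z = 1.036 and the normal density there is 0.233. The information kept relative to the uncut score is 0.233²/(0.15×0.85) = 0.43. A latent correlation of 0.3 shrinks to 0.3×√0.43 = 0.196. The real MARS-5 score has a ceiling and carries less than an uncut normal score, so the true loss is smaller than this implies. The simulation allows for the ceiling.

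**Simulation.** Inputs from the document: n = 100 or 80 and 85% above 22. Assumed, because the document gives no figure: latent correlation ρ between one continuous predictor and adherence of 0.2 to 0.4, and 30% to 80% of participants scoring 25. The full score was tested by rank correlation and the >22 cut by a rank test, both two-sided at 5%, with 4,000 runs per cell (standard error at most √(0.25/4000) = 0.8 points).

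Power in %, full score vs cut, n = 100 (loss in points, computed before rounding):

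| Share scoring 25 | ρ = 0.2 | ρ = 0.3 | ρ = 0.4 |
|---|---|---|---|
| 30% | 45.9 vs 24.9 (21.0) | 80.4 vs 48.0 (32.4) | 96.7 vs 72.8 (23.9) |
| 50% | 40.2 vs 24.9 (15.3) | 75.0 vs 47.7 (27.3) | 95.1 vs 73.8 (21.3) |
| 70% | 35.1 vs 23.4 (11.6) | 64.4 vs 46.7 (17.8) | 88.3 vs 72.7 (15.6) |
| 80% | 26.3 vs 22.5 (3.8) | 56.9 vs 48.5 (8.4) | 82.5 vs 74.0 (8.4) |

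At n = 80 and ρ = 0.3 the figures run from 69.6 vs 39.1 (30% scoring 25) to 48.5 vs 40.2 (80%). Over the whole grid, both sample sizes included, the loss is 3.8 to 32.4 points, and the cut never did better. A second simulation, with MARS-5 in five ordered groups and 45% to 75% of participants at 25, gave 46–48% for the cut against 61–77% for the full score at n = 100, ρ = 0.3.

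**The case against.** The strongest reply is that the association paragraph does not itself name the binary variable. The article condenses a longer plan, and the form and model of an additional analysis commonly go into a statistical analysis plan. The dichotomous wording under Sample size concerns change within participants. Part of this stands: that the associations use only the cut is an inference. It remains the natural one, because the Medication adherence section fixes the cut without exception and no other form is described.

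The sentence can also be read with beliefs as the outcome. Then associations of beliefs with age, sex or number of medications do not involve adherence, and the 15 does not limit them. That stands. It does not rescue the link between beliefs and adherence: comparing belief scores between about 15 and 85 people is the same rank test with the same loss.

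The size of the loss depends on assumptions from outside the document, including a steady latent relation that favours the full score. If beliefs differed mainly around the cut, the gain could shrink. That stands too.

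A reader might be tempted to go further in three ways that the document does not support:
- That a joint logistic model would have too few non-adherent participants per term. No such model is planned.
- That the analysis breaks down at the end of the study, with 5% non-adherent. No association analysis at that time point is stated.
- That a real link would usually be missed. At ρ = 0.4 and n = 100 the cut still has about 73% power.

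**Conclusion.** The point holds in a limited form. As written, the plan leads to a weaker analysis of adherence against beliefs, and against age, sex and number of medications if adherence is the outcome. The group of about 15 follows from the protocol's own figures. That the cut costs power held in every scenario tried; the size, about 4 to 32 points, is conditional on the assumed correlation and score distribution. The primary outcome and the sizing of the study are untouched, and these associations are not among the stated objectives. This is a worthwhile improvement to a supplementary analysis, not a flaw in the main design.

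**What to change.** In Data analysis and statistics, state that association analyses involving self-reported adherence use the full MARS-5 score with rank or ordinal methods, for example Spearman correlation for single factors, or a proportional-odds model with sparse low scores grouped. Keep the >22 cut for the before-after proportion, and report the binary association as a supportive result.

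This costs one sentence and no further data, since all five items are already collected. The small downside is that the main estimates become correlations or cumulative odds ratios, which compare less directly with studies using the cut; the supportive binary result keeps that comparison available.

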### Pilot testing prior to finalisation of the study protocol

Prior to finalisation of this study protocol, the telepharmacy service was pilot tested to evaluate the feasibility of the study design. The pilot study was conducted at a primary healthcare centre in Västerbotten County, in a municipality with an average population density of less than one inhabitant per km^2^. The study was conducted in collaboration with two PCPs at the healthcare centre. Both PCPs had worked at the healthcare centre for several years, and they were in specialist training to become general practitioners.

The recruitment of study participants was initiated in November 2023. In May 2024, 35 people had received an invitation to participate in the pilot study. Ten people gave their written consent to participate. However, two people withdrew their consent during their first contact with the clinical pharmacist. One person misinterpreted the participant information and the other declined due to the use of digital tools.

#### Pilot study conclusions

The results of the pilot study indicated that the study design was feasible and acceptable. Participants and PCPs expressed positive attitudes towards the telepharmacy service, and no amendments in the study design were made prior to finalisation of this study protocol.

The eligibility criteria remained unchanged, since the aim of this study is to develop and evaluate this service among home-living older adults. Depending on the results of the main study, it could be interesting to investigate the effects of this telepharmacy service among other participant groups in the future.

Laboratory testing prior to the medication review was not incorporated as an additional step in this telepharmacy service. This measure was deemed unnecessary, since it will be detected during the telepharmacy service if relevant laboratory tests are outdated or missing. In such cases, relevant laboratory tests will be ordered and evaluated.

Due to practical difficulties, tripartite meetings were not incorporated in the final study design. Interdisciplinary pharmacist-PCP collaboration is therefore essential to ensure that the participant will be provided with consistent and personalised information.

### Data management

Data will be pseudonymised and stored on hard copies or on a secure file sharing platform. The hard copies will be organised in separate folders for each participant and will be stored in a locked filing cabinet. The filing cabinet is in a locked office at the first author’s university department that is inaccessible to unauthorised individuals. The code key will be stored separately from the source data in another locked filing cabinet. Only the research group will have access to the file sharing platform, the filing cabinets and the final study dataset. In the main study, a confidentiality agreement will be established with an external party who will transcribe the data from the semi-structured interviews.

### Patient and public involvement

Participants in the pilot study were involved in the development of the final study design. Patients and/or the public were not involved in the formulation of the research questions or in the development of the outcome measures. They will not be involved in the dissemination of the study results.

### Ethics and dissemination

Ethical approval has been granted by the Swedish Ethical Review Authority (registration number 2022-03819-01 and 2024-08441-02). In the event of substantial amendments to the study design, the amendments will be reported to the ethics committee for approval prior to being implemented. Participant informed consent is required and all participants in the telepharmacy service will provide written informed consent (online supplemental material 1 (in Swedish)). All individuals who also participate in the semi-structured interviews will provide oral informed consent, and this will be collected during the interview sessions. Participation is voluntary, and the participants have the right to withdraw their consents at any time. In the case of withdrawal from study participation, the service will be stopped, and no additional data will be collected.

The study is registered in the clinical trial registry ClinicalTrials.gov (NCT05629936). The study results will be published in peer-reviewed journals and presented at national and international conferences. The results will be presented at group level, and it will not be possible to relate data to any specific individual. Individual participant data will not be shared or publicly available due to privacy and ethical restrictions.

## Discussion

This protocol describes a telepharmacy service in primary care in Northern Sweden’s rural areas, a novel intervention that has not been carried out in this setting before. Development and introduction of telepharmacy services can hopefully help tackle the unequal access to healthcare services that can exist between urban and rural areas. This study aims to provide insights regarding the prevalence of MRPs within this population of home-living older adults. A collaborative approach will be used to identify and resolve potential MRPs, with clinical pharmacists contributing as part of the healthcare team. The findings may provide additional support for continued implementation of clinical pharmacy services within Swedish primary care.

Despite its strengths, this study is subject to some limitations. The absence of a control group hinders between-group comparisons. The single-arm design is still considered a suitable choice for obtaining initial insights into our telepharmacy service. Depending on the results of this study, it may be warranted to conduct robust and high-quality studies in the future to verify the initial findings. Insights from the pilot study suggest that this project may face difficulties in participant recruitment. However, through collaboration with several healthcare centres, the desired sample size is expected to be reached. The reason for non-participation is unclear, and it cannot be ruled out that those who participate differ from those who decline. Lastly, self-report questionnaires will be used to detect intra-individual changes in participants’ medication adherence, health-related quality of life and beliefs about medicines. It is important to acknowledge the potential issues with response bias and that medication adherence, health-related quality of life and beliefs about medicines are all multifaceted phenomena where several factors may contribute to the observed effects.
